## Introduction

 Postsurgical hypoparathyroidism (PoSH) is an iatrogenic condition that occurs as a complication of several different procedures. Thyroid surgery is the most common procedure associated with PoSH, and this is performed for a range of benign and malignant conditions (including multinodular goitre, hyperthyroidism, thyroid cancer). Over 12 000 thyroid operations are done annually in England alone (Hospital Episode Statistics (HES)), a significant proportion of which involves bilateral thyroid surgery, which carries an increased risk of this complication. The volume of thyroid surgery is increasing in the UK^1^ and worldwide, and so occurrence of PoSH is likely to increase. The prevalence of the problem is estimated to be around 22 per 100 000 in the Western world.^2 3^

PoSH has significant short- and long-term morbidity. In the short term, the condition can lead to troublesome symptoms including paraesthesia, spasms of extremities and larynx, anxiety, sensory disturbances, heart dysfunction and tetanic cramps. Its occurrence can prolong hospital stay^4^ and is associated with multiple hospital attendances, readmission to hospital,^5^ ongoing monitoring and treatment—all significantly increasing cost. In the long term, PoSH can cause a wide range of symptoms, a ‘high burden of illness’^6^ and a negative impact on different aspects of quality of life.^7^ Epidemiological studies have also shown that affected individuals have an increased risk of renal impairment, seizures, infections, depression and calcifications.^2 8^ A significant reduction in the incidence of PoSH would therefore have potential to significantly reduce morbidity and associated costs.

Although much research has focused on the incidence,^9^ prevalence^2 3 10^ and factors predisposing to this condition,^11^ reliable preventative measures have not been developed. Many alternative techniques have been explored in the literature. However, the effectiveness of these measures were summarised in a review^9^ showing that although temporary hypocalcaemia rates may be reduced, the impact on long-term PoSH is minimal.

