### Statistical considerations and analyses

#### Sample size

Bayesian optimisation^24 25^ was used to determine the combination of total sample size, phase II sample size and the decision boundaries for the test statistics at the phase II and phase III analyses (Z_II_ and Z_III_ in figures2  3) that minimise the expected sample size required while maintaining an overall significance level of 5% and overall power of at least 80%. Each design explored during the optimisation process was estimated empirically via simulations, using 1000 repeats, and the operating characteristics of this chosen optimal design were re-evaluated using 100 000 repeats. The chosen design has an overall type I error rate of 4.83% and achieves an overall power of 89.33%.

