**Figure 3 F3:**
[figure not shown]
Operating characteristics of the proposed design under the alternative hypothesis.

The target sample size is 454 patients (227 per treatment group), with an interim phase II analysis after 200 patients (100 per treatment group), to allow the trial to stop early due to futility. Assuming a 6-month PoSH rate of 10% in the control group, and 1-day hypocalcaemia rate of 25% and 12.5% in the control and the NIRF+ICG groups, respectively, this design yields around 89% power at the 5% level of significance to detect a relative reduction in 6-month PoSH of at least 70% (ie, a reduction to 3% 6-month PoSH in the NIRF+ICG group), allowing for a 10% drop-out rate. Additionally, this sample size estimate relies on the key assumption that patients who are not hypocalcaemic at 1 day postsurgery will not experience PoSH at 6 months.

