#### Interim analysis (phase II analysis)

Only the phase II primary endpoint will be assessed at the phase II analysis.

The phase II analysis will compare the 1-day hypocalcaemia rates between the arms using multilevel logistic regression, incorporating random effects with respect to surgeon and adjusting for the minimisation factors. At the phase II analysis, the trial will continue only if there is sufficient evidence of superiority of the experimental treatment compared with the control. This will be determined via a one-sided critical region for Z_II_, the Z-value from the multilevel logistic regression model’s Wald test of the adjusted log-odds ratio of 1-day hypocalcaemia. If Z_II_<−0.84162, then the trial will continue; otherwise, it will stop for futility. This decision boundary is equivalent to testing using a one-sided 20% significance level at the phase II analysis. The trial is designed based on a binding stop/go decision.

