#### Final analyses (phase III analyses)

The primary phase III analysis will compare 6-month PoSH rates between the arms using multilevel logistic regression incorporating random effects with respect to the surgeon and adjusting for the minimisation factors. At the phase III analysis, evidence of a difference between the treatment groups will be determined via a two-sided critical region for Z_III_, the Z-value from the multilevel logistic regression model’s Wald test of the adjusted log-odds ratio of the 6-month PoSH. If |Z_III_|>1.28155, then the trial will conclude that there is a significant difference between the treatment arms. This decision boundary is equivalent to testing using a two-sided 20% significance level.

Secondary endpoints with binary measures will be analysed using multilevel logistic regression adjusting for the minimisation factors, incorporating random effects with respect to surgeon. Secondary endpoints with continuous measures will be analysed using multilevel generalised linear models incorporating random effects with respect to surgeon and assuming normal errors at the patient level. If the assumption of normal errors is clearly violated by the observed response data, then transformations of the response variable as well as alternative distributional assumptions will be explored, and the choice of a transformation and/or alternative distribution will be driven by comparative measures of model fit. Models for endpoints that are measured at multiple time points will also include an additional level to account for repeated measures, so that longitudinal effects can be assessed.

The mechanism of the NIRF+ICG intervention and how treatment-related decision-making is affected will be investigated using exploratory methods looking at the effects of the key surgical components identified in the embedded process evaluation.

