## Discussion

Technology in surgery is often incorporated into clinical practice in the absence of good quality evidence to support its effectiveness. RCTs are few and only a minority of surgical interventions have traditionally been based on RCT evidence.^26^,^28^ The challenges in detailed and comprehensive evaluation of surgical techniques and technologies have been well documented.^29^ The need to evaluate surgical technology prior to its introduction into routine clinical practice is now recognised, and this is now encouraged and facilitated by the introduction of the IDEAL framework.^30 31^

Several technologies and surgical approaches have been evaluated for their effectiveness in reducing the risk of PoSH after thyroid surgery. The focus of such interventions has been to help the surgeon identify and preserve the viability of parathyroid glands during the resection of the thyroid. Following initial reports of parathyroid fluorescence at certain wavelengths of light without exogenous fluorophores^32^,^34^ and reports of the fluorescent guiding potential of some chemicals already in clinical use (such as methylene blue and ICG),^35^ a number of case reports and series have demonstrated the potential utility of fluorescent guided identification and preservation of parathyroid glands during thyroidectomy.^36^ Some randomised trials have now demonstrated that use of autofluorescence and ICG-based fluorescence reduce the number of inadvertently resected parathyroid glands, increase postsurgical PTH levels, reduce postsurgical hypocalcaemia rates and the need for treatment; however, the impact on long term PoSH has not been convincingly demonstrated.^37 38^

NIFTy is the first UK multicentre trial in thyroid surgery. The trial aims to both assess the mechanisms by which fluorescent imaging reduces PoSH and to pragmatically evaluate the effectiveness of the technology in a range of centres and across a number of different thyroid surgeons.

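### The 5% overall significance level stated for 6-month PoSH holds only if NIRF+ICG gives no benefit on 1-day hypocalcaemia; with an early benefit and no PoSH effect the error is about 10-18% two-sided, or 8-10% for false claims of benefit

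*Protocol article*

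**What the plan says.** The Sample size section says the design was optimised "while maintaining an overall significance level of 5% and overall power of at least 80"%, and reports: "The chosen design has an overall type I error rate of 4.83% and achieves an overall power of 89.33"%. After Figure 3 the same section ties this level to the primary endpoint: "this design yields around 89% power at the 5% level of significance to detect a relative reduction in 6-month PoSH of at least 70"%.

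The level is built from two tests on two endpoints.

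- Interim analysis (phase II analysis): 1-day hypocalcaemia only, continue if Z_II<−0.84162. "This decision boundary is equivalent to testing using a one-sided 20% significance level at the phase II analysis", and "The trial is designed based on a binding stop/go decision".
- Final analyses (phase III analyses): 6-month PoSH, significant difference if |Z_III|>1.28155. "This decision boundary is equivalent to testing using a two-sided 20% significance level".

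The visible text does not say which null hypothesis 4.83% refers to.

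**The concern.** The null for the primary question is that NIRF+ICG does not change PoSH. That null is compatible with a real reduction in 1-day hypocalcaemia. If there is such a reduction, the trial passes the interim test more often than the 20% on which the overall level relies, and PoSH is then tested at close to 20%.

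The article makes this situation a live one. The Introduction says of other preventive techniques that "although temporary hypocalcaemia rates may be reduced, the impact on long-term PoSH is minimal". The Discussion says that randomised trials of fluorescence have shown less postsurgical hypocalcaemia; "however, the impact on long term PoSH has not been convincingly demonstrated". Phase III exists to tell an early effect from a lasting one, and the stated 5% does not cover the case of an early effect alone.

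A reader would take a significant PoSH result as a 5% finding. Yet 12/204 against 20/204 PoSH events, with a nominal p of about 0.145, would meet the rule.

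**Working it through.** **Inputs, all from the article.** 227 per arm, 100 per arm at the interim, 10% drop-out (227 × 0.9 ≈ 204 per arm at 6 months). Control rates: hypocalcaemia 25%, PoSH 10%. Alternative: 12.5% and 3%. PoSH arises only in patients hypocalcaemic on day 1. Boundaries −0.84162 and ±1.28155.

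**Statistic.** For a/n₁ against c/n₀ events, Z = ln{[a/(n₁−a)]/[c/(n₀−c)]} / √[1/a + 1/(n₁−a) + 1/c + 1/(n₀−c)]. A false positive is Z_II<−0.84162 together with |Z_III|>1.28155 when the PoSH rates are equal.

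**Step 1: reproduce the stated figures** (simulation, 400,000 repeats).
- Power at 25%/12.5% and 10%/3%: 89.3-89.4% (stated 89.33%).
- Type I error with no effect on either endpoint: 4.6% with drop-out, 4.7% without (stated 4.83%).

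Bivariate-normal check. With PoSH nested in hypocalcaemia, the patient-level correlation is √[0.10×0.75/(0.25×0.90)] = 0.577. Without drop-out, corr(Z_II, Z_III) = 0.577×√(100/227) = 0.383. This gives 4.28% (benefit) + 0.53% (harm) = 4.81%; with drop-out it gives 4.72%. Independent tests would give 0.20×0.20 = 4%, and the positive correlation supplies the rest. So 4.83% matches the null of no effect on both endpoints.

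**Step 2: chance of continuing when there is an early effect.**
- Hypocalcaemia 20%: the log-odds ratio is ln(0.20/0.80)−ln(0.25/0.75) = −0.288, with SE √(1/20+1/80+1/25+1/75) = 0.340, so the mean of Z_II is −0.845. P(continue) = Φ(−0.842+0.845) ≈ 50%.
- Hypocalcaemia 12.5%: −0.847/0.380 = −2.23, so P(continue) ≈ Φ(1.39) ≈ 92% (93% in simulation).

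**Step 3: error on PoSH, 10% in both arms** (simulation, 10% drop-out, control hypocalcaemia 25%).

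| NIRF+ICG 1-day hypocalcaemia | P(continue) | Significant, either direction | False benefit only |
|---|---|---|---|
| 25% | 20% | 4.6% | 4.1% |
| 22.5% | 34% | 7.2% | 6.0% |
| 20% | 51% | 10.0% | 7.7% |
| 17.5% | 68% | 12.9% | 9.0% |
| 15% | 83% | 15.5% | 9.6% |
| 12.5% (the plan's assumption) | 93% | 17.6% | 9.9% |

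The ceilings are the final test's own levels: 20% two-sided and 10% for benefit. If hypocalcaemia instead rose to 30%, the two-sided rate would be about 1.4%.

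**Step 4: sensitivity.** Allowing PoSH outside the 1-day hypocalcaemic group gives 10.1% to 18.0% over the range 20% to 12.5%. PoSH of 5% in both arms gives 10.0% and 17.8% at the two ends.

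**Step 5: the example.** For 12/204 against 20/204, OR = (12/192)/(20/184) = 0.575, ln OR = −0.553, SE = √(1/12+1/192+1/20+1/184) = 0.379. Z = −1.46, p ≈ 0.145, 95% CI for the OR 0.27 to 1.21. Because 1.46>1.28155, the rule calls this significant.

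**The case against.** - **The joint null is a recognised definition.** Defining type I error under no effect on either endpoint is a known choice for seamless designs with a surrogate, both 20% levels are openly stated, and Figure 2, on the null hypothesis, cannot be seen. This stands as a defence of the design. It does not make 5% the error rate for PoSH alone, which is how the text after Figure 3 presents it.
- **A reader might infer two to nearly four times the stated risk of wrongly claiming prevention.** That multiple (10.0/4.83 = 2.1 to 17.6/4.83 = 3.6) counts false conclusions of harm as well. False claims of benefit are 7.7-9.9%, which is 1.9 to 2.4 times the 4.1% under no effect on either endpoint.
- **The upper end is demanding under the plan's nesting assumption.** With hypocalcaemia at 12.5% and PoSH at 10%, 10/12.5 = 80% of hypocalcaemic NIRF+ICG patients would progress, against 10/25 = 40% of controls. This stands. At 20% the figure is 10/20 = 50%, which is less extreme, and the error is already 10%.
- **A reader might infer that the article concedes fluorescence does not lower PoSH.** It does not. The Introduction sentence concerns other techniques, and the Discussion reports a lack of convincing proof, not a lack of effect.

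**Conclusion.** The concern holds in this form: 4.83% is the error rate when NIRF+ICG affects neither endpoint, and the 5% bound on PoSH is secured only when there is no beneficial effect on 1-day hypocalcaemia. For relative reductions of 20-50% in early hypocalcaemia with PoSH unchanged, the two-sided error is about 10-18% and false benefit about 8-10%. A 10% relative reduction gives about 7% and 6%.

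The calculation omits the surgeon random effect and the covariates, whose variances the article does not give. The close match to both stated figures suggests that this matters little.

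A reader might also conclude that the boundary of 1.28155 has to be replaced. The document does not support that: sample sizes and boundaries were optimised together, and a stricter boundary trades error against power. What is wrong as written is the error rate attached to the PoSH comparison.

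**What to change.** In the Sample size section, including the power statement after Figure 3:

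1. State that 4.83% applies to the null of no effect on both 1-day hypocalcaemia and PoSH.
2. Add the PoSH-specific rates for an early effect without a PoSH effect: about 10-18% two-sided (ceiling 20%) and about 8-10% for false benefit (ceiling 10%), for hypocalcaemia falling from 25% to between 20% and 12.5%.
3. Do not describe |Z_III|>1.28155 as significance at the 5% level for PoSH.
4. Commit to reporting the nominal p-value and 95% CI beside the phase III decision.

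This costs wording only. The downside is a less favourable stated error rate.

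The sponsor may also consider a stricter final boundary with no extra patients, though this is not required. A boundary of 1.96 holds PoSH error at or below about 5% whatever the early effect (3.9% at 12.5% hypocalcaemia), with power of about 78%, below the plan's own 80% floor. A boundary of 1.87 gives about 5.0% at the assumed early effect and 5.4% if hypocalcaemia falls to 10%, with power of about 80.6%. With either, the stated power would need restating.

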#### Phase III secondary outcome measures

To compare NIRF+ICG and standard care in terms of:

Transient hypocalcaemia.Protracted hypoparathyroidism, defined as either an adjusted calcium of <2.1 mmol/L or the need for calcium and/or vitamin D supplements to treat symptoms or maintain adjusted calcium in the low normal range at 1 month post-surgery.Intra-operative complications graded using the ClassIntra classification.^22^Postoperative complications within 6 months of operation graded using the Clavien-Dindo classification.^23^Length of hospital stay in days post-surgery.Health related quality of life (HRQoL) at baseline, 1–6 months postoperation using the Short Form 36 Health Survey Questionnaire and Hypoparathyroid Patient Questionnaire instruments.Any episode of readmission to hospital within 6 months of operationHypercalcaemia occurring within 6 months of operation, defined as any adjusted calcium >2.6 mmol/L measured at 1 day, 1 month and 6 months post-surgery.

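### If the trial passes phase II, the phase III estimate for transient hypocalcaemia reuses the 200 participants selected on that same outcome, and is shifted towards NIRF+ICG when the true effect is null or modest

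*Protocol article*

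**What the plan says.** Four parts of the protocol article bear on this.

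- **Phase II primary outcome measure.** Transient hypocalcaemia is an adjusted calcium below 2.1 mmol/L on the day after surgery.
- **Interim analysis (phase II analysis).** On this outcome, "the trial will continue only if there is sufficient evidence of superiority of the experimental treatment". The criterion is Z_II < -0.84162, a one-sided 20% test, and the stop/go decision is binding.
- **Phase III secondary outcome measures.** The same outcome heads the list: "Transient hypocalcaemia.Protracted hypoparathyroidism, defined as" and so on. It is also named among the phase III secondary objectives.
- **Final analyses (phase III analyses).** "Secondary endpoints with binary measures will be analysed using multilevel logistic regression adjusting for the minimisation factors", with random effects for surgeon.

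The Sample size section sets the total at 454 and counts the 200 interim participants (100 in each group) within it. The article does not say which participants enter the phase III comparison of transient hypocalcaemia. The Analysis methods section leaves populations to the statistical analysis plan, which is not at hand.

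**The concern.** The phase III analyses take place only if the first 200 participants already favoured NIRF+ICG on 1-day hypocalcaemia by a set margin. An ordinary logistic model fitted to all 454 treats those 200 as an unselected sample. Among trials that reach phase III, its odds ratio, interval and p-value therefore lean towards NIRF+ICG.

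Interpretation is what is at stake. The trial sets out to explain mechanism, and its sample size assumes that PoSH arises only in patients who are hypocalcaemic on day 1. Readers will be inclined to take a favourable day-1 result at phase III as separate support for that pathway, although the continuation rule has partly secured it. The Discussion says that earlier trials reduced early hypocalcaemia without convincingly showing an effect on long-term PoSH. An overstated early effect next to an uncertain PoSH result is thus a realistic outcome.

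**Working it through.** **Inputs from the article.** 100 per group at phase II and 227 per group in total, hence 127 per group afterwards. Boundaries Z_II < -0.84162 and |Z_III| > 1.28155. Rates: "Assuming a 6-month PoSH rate of 10% in the control group, and 1-day hypocalcaemia rate of 25% and 12.5% in the control" and NIRF+ICG groups respectively; "a reduction to 3% 6-month PoSH in the NIRF+ICG group"; "allowing for a 10% drop-out rate". PoSH occurs only among those hypocalcaemic at day 1.

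**Step 1: reproduce the stated design.** A two-stage simulation with unadjusted Wald tests (400,000 repeats) gives power of 89.5%; the article states 89.33%. Overall type I error is 4.72% with dropout at 6 months only and 4.84% with dropout at phase II as well; the article states 4.83%. The simplified model therefore represents the design adequately.

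**Step 2: analytic check with no true effect, 25% in both groups.**

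- Mean of Z_II given continuation: -φ(0.84162)/0.20 = -1.400.
- SE of the log odds ratio in the first 200: √[2 × (1/25 + 1/75)] = 0.327.
- Shift in the first 200: 1.400 × 0.327 = 0.457 on the log scale.
- Share of the pooled data: 200/454 = 0.44.
- Shift in the pooled estimate: 0.457 × 200/454 = 0.201, so the odds ratio is exp(-0.201) = 0.82.
- In units of the pooled SE: 1.400 × √(200/454) = 1.400 × 0.664 = 0.93.

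**Step 3: simulation of the pooled estimate given continuation** (control rate 25%, complete day-1 data; ranges reflect whether 0.5 was added to the cells).

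| NIRF+ICG rate | P(continue) | True OR | Pooled OR given continuation |
|---|---|---|---|
| 25% | 20% | 1.00 | 0.82 |
| 22% | – | 0.85 | 0.73 |
| 20% | 51% | 0.75 | 0.66–0.67 |
| 15% | 83% | 0.53 | 0.50 |
| 12.5% (design) | 93% | 0.429 | 0.414–0.418 |

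In the null row the risk difference is -3.8 points instead of 0, the 95% interval covers the truth in about 90% of continuing trials, and Z < -1.96 occurs in about 10% instead of 2.5%. In the design row coverage is 96.3%. Part of the small gap there is ordinary small-sample bias of the log odds ratio, since without a continuity correction the mean is already 0.4245 with no selection.

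**Step 4: participants randomised after the first 200 (127 per group).** With no true effect, given continuation: odds ratio 1.00, false benefit 2.4%, coverage 95%. The SE is larger by √(454/254) = 1.34.

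**Step 5: unconditional error.** The chance, with no true effect, of both continuing and then finding Z < -1.96 in the pooled data is about 0.197 × 0.102 = 2.0%, which is below 2.5%.

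**Step 6: accuracy given continuation** (root mean squared error of the log odds ratio, pooled against later participants only): null 0.270 against 0.291; 22% 0.239 against 0.296; 20% 0.227 against 0.303; 12.5% 0.243 against 0.341. The pooled estimate is the more accurate in every scenario, despite its bias.

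**The case against.** Several objections have force.

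- **Population not stated.** Use of all 454 is inferred, and the article defers populations to the analysis plan. That stands as a qualification. However, the article itself fixes the model for binary secondary endpoints and makes no exception for the one that decides continuation. Pooling is also the natural reading of a seamless 454-patient trial.
- **The bias exists only given continuation.** This is correct. A reader might infer that the design inflates false claims on hypocalcaemia or that reports of it are biased towards NIRF+ICG without qualification. The documents do not support either. Unconditional error is 2.0%, and a stopped trial would also have a day-1 result to report. If stopped trials report their 200 and continuing trials all 454, the average odds ratio is 1.05, 0.81 and 0.44 for true values of 1.00, 0.75 and 0.43, so across all reports the lean is slightly against NIRF+ICG.
- **Negligible at the design effect.** Also correct. But that effect is an assumption, and the shift matters if the true effect is smaller. Even with no effect, about 90% of continuing trials would not reach nominal significance.
- **Using only later participants discards data.** This stands against replacing the pooled estimate, whose error is lower throughout. It does not count against showing both.

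**Conclusion.** The point holds as a minor reporting matter for one secondary outcome. Given continuation, and if all 454 are analysed, the ordinary logistic estimate for transient hypocalcaemia is shifted towards NIRF+ICG. The shift is about 0.9 SE when there is no true effect, shrinks as the true effect grows, and is negligible at 25% against 12.5%.

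Two further inferences are tempting and should not be drawn. First, the primary PoSH decision is not compromised, because its boundary was chosen and simulated jointly with the phase II rule. Second, a separate correction for day-1 PTH is not warranted. Its size would rest on an assumed correlation with hypocalcaemia, and the article analyses PTH over 6 months in a repeated-measures model.

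The figures assume a 25% control rate and complete day-1 data, and they leave out surgeon effects and minimisation covariates.

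**What to change.** In the Final analyses section, or in the analysis plan, add for transient hypocalcaemia:

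- the all-participant estimate is retained and labelled as conditional on passing the phase II rule;
- its p-value is not presented as independent confirmation of an early effect;
- the estimate from participants randomised after the 200 used at phase II (454 - 200 = 254) is reported beside it.

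An estimate of the PoSH effect adjusted for the phase II selection could be added but is optional; the PoSH decision itself stays on all participants.

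The cost is one extra model fit and a less precise companion estimate, with an SE about 1.3 times larger. No new data or participants are needed.

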### Randomisation and blinding

Following confirmation of written informed consent and eligibility, participants will be randomised into the trial. Randomisation will be performed centrally using the central automated 24-hour randomisation system. Participants will be randomised on a 1:1 basis to receive thyroid surgery performed either as per standard care or with NIRF+ICG and allocated a unique trial number. A computer-generated minimisation programme that incorporates a random element will be used to ensure treatment groups are well-balanced for the following participant characteristics: operating surgeon, indication (Graves’ disease, cancer, etc) and sex. Clinical assessments and baseline questionnaires will be completed before randomisation. Treatment allocation will not be blinded to participants, medical staff or clinical trial staff.

The timing of clinical assessments and data collections points are summarised in table 2.

**Table 2 T2:** Clinical assessments and data collection timepoints

Events	Baseline/preop	Surgery	1 day post-op	1 month post-op	6 months post-op
Clinical assessments/investigations					
Clinical examination	**✓**		**✓**	**✓**	**✓**
Biochemistry	**✓**		**✓**	**✓**	**✓**
Trial consent	**✓**				
Operative details		**✓**			
Complications		**✓**		**✓**	**✓**
Data collection time points					
Eligibility eCRF	**✓**				
Randomisation eCRF	**✓**				
Baseline eCRF	**✓**				
Operative eCRF		**✓**			
1 day after surgery f/up eCRF			**✓**		
1 month after surgery f/up eCRF				**✓**	
6 months after surgery f/up eCRF					**✓**
HRQoL					
SF-36	**✓**			**✓**	**✓**
HPQ-28	**✓**			**✓**	**✓**

eCRFelectronic case report formHPQ-28Hypoparathyroid Patient QuestionnaireHRQoLhealth related quality of lifeSF36Short Form 36 Health Survey Questionnaire

Preoperative investigations and preparation will be as per institutional protocol. A biochemical assessment will be carried out including thyroid function, renal function, calcium, PTH, vitamin D, magnesium, phosphate, and urea and electrolytes, details of which will be recorded on the trial case report forms (CRFs). Participants must not be given prophylactic treatment with calcium and/or active vitamin D supplements perioperatively. However, any vitamin D deficiency that is detected during investigation may be treated as per local protocols.

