#### Phase III key secondary outcome

Postoperative PTH over 6 months, measured at 1 day, 1 month and 6 months postsurgery.

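### As written, the model for continuous secondary endpoints (PTH, SF-36, HPQ-28) names no adjustment for indication, sex or the collected baseline value, and so gives up precision at no saving

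*Protocol article*

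**What the plan says.** All statements below are from the protocol article.

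- **Binary secondary endpoints** (Final analyses): "Secondary endpoints with binary measures will be analysed using multilevel logistic regression adjusting for the minimisation factors, incorporating random effects with respect to surgeon". The phase II primary model (Interim analysis) and the phase III primary model (Final analyses) carry the same adjustment.
- **Continuous secondary endpoints** (Final analyses, the next sentence): "Secondary endpoints with continuous measures will be analysed using multilevel generalised linear models incorporating random effects with respect to surgeon and assuming normal errors". No covariate is named.
- **Repeated measures** (Final analyses): "Models for endpoints that are measured at multiple time points will also include an additional level to account for repeated measures". The role of a baseline measurement is not given.
- **Minimisation factors** (Randomisation and blinding): operating surgeon, indication and sex.
- **Baseline data** (Randomisation and blinding): "A biochemical assessment will be carried out including thyroid function, renal function, calcium, PTH, vitamin D" and further analytes, before surgery. Table 2 shows SF-36 and HPQ-28 at baseline, and the text places the baseline questionnaires before randomisation.
- **Key secondary outcome**: "Postoperative PTH over 6 months, measured at 1 day, 1 month and 6 months postsurgery". Baseline is not part of it.
- **Quality of life** (Phase III secondary outcome measures): "Health related quality of life (HRQoL) at baseline, 1–6 months postoperation". Here baseline is listed within the outcome.
- **Deferral** (Analysis methods): all analyses are to be predefined in the statistical analysis plan.

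**The concern.** The article names the adjustment for the phase II primary, phase III primary and binary secondary models. It does not name it for the continuous ones. A statistician following the text would fit PTH, SF-36 and HPQ-28 with a surgeon random effect and neither indication nor sex, and would give the collected baselines no role.

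Two separate losses follow.

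1. Minimisation balances the arms on indication and sex. If these predict the outcome and are left out, their variation stays in the residual although the design has already removed most of it from the treatment difference. The reported standard errors then tend to be too large, that is, conservative.
2. A baseline value that correlates with follow-up explains part of the outcome variance. Leaving it out gives a valid but wider interval than the data allow.

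The endpoints affected include the designated key secondary outcome. The role of baseline is also left uneven: PTH is defined after surgery only, while HRQoL lists baseline among its time points.

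**Working it through.** **The plan's own figures.** The article states no precision or power for any continuous endpoint. Its overall power of 89.33% and type I error of 4.83% concern the binary primary outcome. A simulation of the two-stage design (400,000 repeats, no surgeon effects, complete 1-day data, 10% loss by 6 months) gives 89.3% power. The type I error is 4.67% to 4.89% across loss assumptions, close to the stated value. None of this bears on the continuous models.

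**Inputs.**
- 227 per arm and 10% drop-out (Sample size): 227 × 0.9 = 204.3, taken as n = 204 per arm.
- Outcome SD set to 1, so effects are in SD units (assumption).
- Baseline-to-follow-up correlation r = 0.3, 0.5 or 0.7 (assumption; the article gives none).
- Share of variance explained by indication and sex, R² = 2%, 5% or 10% (assumption).

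**Baseline adjustment.** Without it, SE = √(2/204) = 0.0990 SD. With it, SE = √(2(1 − r²)/204), so the SE is multiplied by √(1 − r²) and the effective n per arm is 204/(1 − r²). Power is Φ(0.25/SE − 1.96) for an illustrative difference of 0.25 SD, two-sided 5%.

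| r | 1 − r² | SE factor | SE | Effective n per arm | Power, 0.25 SD |
|---|---|---|---|---|---|
| no adjustment | 1 | 1 | 0.0990 | 204 | 71.4% |
| 0.3 | 0.91 | 0.954 | 0.0945 | 224 | 75.4% |
| 0.5 | 0.75 | 0.866 | 0.0857 | 272 | 83.0% |
| 0.7 | 0.51 | 0.714 | 0.0707 | 400 | 94.2% |

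**Indication and sex.** The SE is multiplied by √(1 − R²): √0.98 = 0.990, √0.95 = 0.975, √0.90 = 0.949. That is a cut of about 1% to 5%. It multiplies with the baseline factor only if R² is read as a share of the variance left after baseline adjustment.

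**Baseline as a response.** Take a model for baseline, 1 month and 6 months with equal correlations between visits, one common baseline mean for both arms, and a treatment effect at each postoperative visit. Generalised least squares gives a 6-month SE of 0.0945, 0.0857 and 0.0707 at r = 0.3, 0.5 and 0.7. These equal the covariate-adjusted values. Entering baseline as a response is therefore as good as entering it as a covariate, provided the arms are constrained to be equal at baseline.

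**The case against.** The strongest reply is that this is a condensed article which defers its analyses to a statistical analysis plan not shown here. Covariate lists for secondary endpoints commonly sit in that plan, and nothing in the article excludes baseline or the minimisation factors. This stands as a limit on the point: the plan may already contain the adjustment. It does not remove the point, because the article does state adjustment for the other models and words the neighbouring sentence differently. The model it does state can be improved at almost no cost.

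Three stronger readings are tempting, and the article supports none of them.

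- *That the continuous models ignore the minimisation factors altogether.* They do not. Operating surgeon is one of the three factors and enters as a random effect. Only indication and sex are unnamed.
- *That baseline HRQoL will be analysed as an outcome under one treatment term, which would dilute the effect.* A single term over baseline, 1 month and 6 months would estimate a constant effect at 0.667 of its size. The article specifies no such model. The HRQoL line may only list when the questionnaires are completed, as Table 2 does, and the repeated-measures level is there to assess effects over time. The reading cannot apply to PTH, which is defined after surgery only.
- *That the comparison is biased.* Randomisation protects the estimate. The loss is of precision.

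It is also fair to say that the size cannot be taken from the article, which gives no SD or correlation, and that length of stay has no baseline value to adjust for.

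**Conclusion.** The point holds as a matter of efficiency and consistent wording. As stated, the model for continuous secondary endpoints omits indication, sex and the baseline values that the trial collects for PTH, SF-36 and HPQ-28.

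Under assumed correlations of 0.3 to 0.7, baseline adjustment would lower the standard error by about 5% to 29%. Indication and sex would lower it by about 1% to 5% if they explain 2% to 10% of the variance. The true correlation may differ by instrument and by visit, so these are ranges and not predictions. The primary analyses and the phase II stop/go decision are untouched, since both primary models already adjust for the minimisation factors.

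**What to change.** In Final analyses (phase III analyses), and in the statistical analysis plan if it does not already say so, state that:

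- continuous secondary endpoints are analysed with a surgeon random effect and adjusted for indication and sex;
- where a baseline measure exists (PTH, SF-36, HPQ-28; not length of stay), its value is used either as a covariate or as a response with the arms constrained to be equal at baseline;
- treatment effects are estimated at postoperative visits only: 1 day, 1 month and 6 months for PTH, 1 and 6 months for HRQoL;
- baseline HRQoL, although listed within the outcome, is not pooled into the treatment effect.

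The cost is a few sentences and a rule for missing baseline values. Every variable is already collected, and the sample size, decision boundaries and primary analyses do not change. The wording should be fixed before comparative data are seen, since the trial is unblinded.
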